## Abstract

**Background and purpose:**

Recent research has highlighted non-operative management (NOM) as a viable alternative for frail older adults with hip fractures in the final phase of life. This study aims to guide Dutch physicians and hospitals nationwide in a standardised implementation of shared decision-making regarding surgery or NOM in selected frail older adults with a hip fracture.

**Methods and analysis:**

The patient population for implementation includes frail older adults aged ≥70 years with an acute proximal femoral fracture, nursing home care or a similar level of care elsewhere and at least one additional criterion (ie, malnutrition, severe mobility impairment or ASA≥4). The 2-year implementation study will be conducted in four phases. In phases 1 and 2, barriers and facilitators for implementation will be identified and an implementation protocol, educational materials and patient information will be developed. Phase 3 will involve an implementation pilot in 14 hospitals across the Netherlands. The protocol and educational material will be improved based on healthcare provider and patient experiences gathered through interviews. Phase 4 will focus on upscaling to nationwide implementation and the effect of the implementation on NOM rate will be measured using data from the Dutch Hip Fracture Audit.

**Ethics and dissemination:**

The study was exempted by the local Medical Research Ethics Committee (MEC-2023-0270, 10 May 2023) and Medical Ethics Committee United (W23.083, 26 April 2023). The study’s results will be submitted to an open access international peer-reviewed journal. Its protocols, tools and results will be presented at several national and international academic conferences of relevant orthogeriatric (scientific) associations.

**Trial registration number:**

NCT06079905.

STRENGTHS AND LIMITATIONS OF THIS STUDYThis study builds on an existing foundation of recent well-received (inter)national publications, countrywide initiatives involving shared-decision making and recent demands for assistance in the implementation of non-operative management of hip fractures in selected frail older adults with a limited life expectancy.The study will employ a staged approach in four phases, involving implementation strategies at the individual, local and national level, that range from local educational sessions to nationwide distribution at conferences and proposed guideline changes.The study design allows for regular adjustment of its implementation protocols and educational materials based on patient and healthcare provider feedback from interviews from 14 different hospitals throughout the Netherlands.While the study has an ambitious 2-year time scheme to achieve nationwide implementation in the hospital setting, it will provide an important foundation for further initiatives.

## Introduction

A hip fracture in frail older adults can indicate an approaching end of life. Advanced age, multiple comorbidities and severe mobility limitations are important risk factors for early postoperative mortality after a hip fracture.^1 2^ Studies show that >30% of patients die within 1-year post hip fracture, with 6-month mortality rates in older adults with dementia exceeding 55%, often with low quality of life in the months preceding death.^3–5^ These patients, in their final phase of life, often do not benefit from an operative treatment that aims to restore mobility. Operations are often conducted in this population as a palliative treatment option, focused primarily on pain reduction. Based on these insights, a paradigm shift is occurring in clinical approach, emphasising the importance of individualised care plans focused on optimal quality of life.^6 7^

The FRAIL-HIP study has confirmed that non-operative management (NOM) can be a good alternative to operative management in select frail older adults with a limited life expectancy.^5 8–10^ Quality of life after NOM was valued non-inferiorly and the majority of the next-of-kin rated the quality of dying of their relative as very good.^5 8^ Despite higher mortality rates in patients opting for NOM, the option to allow patients to pass away in a familiar environment was a compelling factor in favour of NOM in this select population.^11^ Both operative and NOM can thus be effective treatment options as part of palliative care in selected frail older adults with a limited life expectancy. Following these results, multiple Dutch hospitals have asked for guidance on implementing NOM in their institutions.

Central to NOM is the shared decision-making (SDM) process, involving patients and their families in treatment decisions aligned with the patients’ preferences and needs. Based on the results of the FRAIL-HIP study and other literature, an implementation protocol has been drafted, piloted and refined based on experiences of healthcare professionals.^7 9 12^ This protocol version will serve as the starting point for the iterative process towards nationwide implementation.

The aim of this study is nationwide implementation of SDM on treatment of hip fractures, involving both NOM and operative treatment, to ensure that frail older adults receive optimal, patient-centred care in the final phase of their lives.

## Methods and analysis

### Study design and aims

This 2-year implementation study will consist of four phases (figure 1): development of the implementation protocol and educational material (phase 1 and 2), implementation across a subset of hospitals across the Netherlands and process evaluation and optimisation of the protocol based on healthcare provider/patient experiences (phase 3) and upscaling towards nationwide implementation and project evaluation (phase 4). The study design of phases 3 and 4 entails a multicentre prospective cohort study. Overall, the project will cover all activities as recommended in the ImpRes Guide, which mentions four implementation phases (ie, exploration, installation, initial implementation and full implementation) and should efficiently translate local knowledge into general knowledge.^13^ The ‘Consolidated Framework for Implementation Research’ (CFIR) was used for designing this project.^14 15^ With education being a critical part of the implementation, elements of the education strategy from Wensing *et al*
16 were added. The CFIR domains that the four phases of this project will cover are mentioned in table 1.

**Figure 1 F1:**
[figure not shown]
Schematic overview of the implementation process in four phases. DHFA, Dutch Hip Fracture Audit; NOM, non-operative management. FRAIL-HIP study^8^

**Table 1 T1:** CFIR domains and their role in the implementation project

CFIR domain	Role in project
Inner setting	Gain insight into the hospital/implementation location, including internal network and communication, culture (norms and values), knowledge, current use of the intervention and implementation climate (tension for change, feedback, learning climate)
Outer setting	Gain insight into the needs of patients/proxies and pressure from peers (need for hospitals to use the same protocol)
Characteristics of individuals	Gain insight into the confidence/preparedness to discuss and apply NOM through SDM with the intended target group
Characteristics of the intervention	Gain insight into the SDM conversation as part of NOM, the needs of healthcare providers on how to conduct SDM and who participates in it, and what they need to apply NOM

CFIR, Consolidated Framework for Implementation Research; NOM, non-operative management; SDM, shared decision-making.

To achieve the primary aim, this study will use a staged approach in four phases that involves three levels: he healthcare provider specific/local hospital level (micro) in phases 1–3, the level of a limited number of hospitals (meso) in phase 3 and the national level (macro) in phase 4. The four consecutive phases of the project have phase-specific aims with corresponding target populations and points of action, that are described in table 2. To ensure nationwide implementation, many parties and interest groups are or will be involved in the project (table 3).

**Table 2 T2:** Study aims with specific action points per targeted group for the four study phases

Points of action per phase	Targeted group	Aim/outcome
**Phase 1**		
Qualitative research on patient experiences and perceived barriers and facilitators for SDM on NOM	Patients, next-of-kin and healthcare providers*	Enriching the implementation protocol with recent research on patient/healthcare provider experiences regarding SDM on NOM versus operative treatment. Providing insight into barriers and facilitators on the local and individual level
**Phase 2**		
Development of educational material on SDM with frail older adults with hip fractures for patients and healthcare providers Implementing SDM on NOM in the curriculum for (orthopaedic) surgeons in training	Patients, next-of-kin and healthcare providers*	Increasing (practical) knowledge on performing SDM on NOM in healthcare providers. Providing healthcare providers with tools to prepare patients and next-of-kin for SDM on NOM vs operative treatment
**Phase 3**		
Presentations of the implementation protocol and included tools at annual meetings of the involved scientific associations	Healthcare providers*, members of associated scientific associations	Creating awareness and a sense of urgency for SDM implementation and identifying local drivers of change for future implementation
Implementation of the NOM implementation protocol and evaluation through interviews with patients and healthcare providers in 14 selected Dutch hospitals	Local project teams and drivers of change in 14 Dutch hospitals and patients/next-of-kin	Evaluating and improving the implementation protocol and educational modules based on local experiences, barriers and facilitators through patient and healthcare provider interviews
**Phase 4**		
Maintaining and improving awareness through conference and regional trauma network presentations Identification of local ambassadors/drivers of change Dissemination of the implementation protocol/educational tools through a dedicated website, scientific publications and media coverage	Healthcare providers*, and specifically, local drivers of change, in all Dutch hospitals treating frail older adults with hip fractures	Upscaling of the implementation to all hospitals in the Netherlands that treat the targeted patient group
Measuring the effect of implementation, changes in NOM rate, through the DHFA database	Dutch patients and hospitals through the DHFA database	Evaluating changes in practice after implementation

*Healthcare providers include (orthopaedic) trauma surgeons, geriatricians, acute care physicians, anaesthesiologists, residents and physician assistants directly involved in (acute) care for frail older adults with a hip fracture in Dutch hospitals.

DHFA, Dutch Hip Fracture Audit; NOM, non-operative management; SDM, shared decision-making.

**Table 3 T3:** Participating parties and their roles and responsibilities

Participator(s)	Roles and responsibilities
Central project group/steering committee	The project group is responsible for the general oversight of the entire project.
Participating hospitals	They will implement the NOM protocol locally, and will provide data needed to evaluate the effect of the implementation. They will need to allow local training and participate in interviews to gain insight into their experience with NOM implementation.
Patients and/or proxies	Will be asked to voluntarily participate in interviews and provide feedback on the chosen treatment and SDM process.
Dutch Hip Fracture Audit (DHFA) and Dutch Institute for Clinical Auditing	They will provide the data so the hospitals can use it as mirror information. The DHFA data (which are existing data) will be used as preimplementation and postimplementation data, and will thus allow accurate monitoring of the impact of NOM implementation.
Scientific associations (Dutch Trauma Society (NVT), Dutch Association of Surgeons of the Netherlands (NVvH), Dutch Orthopaedic Association (NOV) and Dutch Association of Clinical Geriatrics (NVKG))	The scientific associations are responsible for education for medical specialists and residents-in-training. They will play a key role in the education sessions and in forwarding information on our project to their members.
Members of the National Association of General Practitioners (LHV) and the Association for Older Adult Care Physicians (Verenso)	Will be kept informed about this project through mailings and presentations during their annual conferences.

LHV, Landelijke Huisartsen Vereniging; NOM, non-operative management; NOV, Nederlandse Vereniging voor Orthopedie; NVKG, Nederlandse Vereniging voor Klinische Geriatrie; NVT, Nederlandse Vereniging voor Traumachirurgie; NVvH, Nederlandse Vereniging voor Heelkunde; SDM, shared decision-making.

### Study population

Phases 1 and 2 will not include patients or patient data but will include healthcare provider and patient association perspectives. Phases 3 and 4 will also include frail older adults with a limited life expectancy who sustained a proximal femoral fracture. Patients will be included and receive SDM on NOM and operation if they meet the following criteria:

Acute proximal femoral fracture (AO type 31), confirmed on X-ray or CT scan.70 years or older.Living in a nursing home or receiving similar care at home.And at least one of the following characteristics:Malnutrition (cachexia or body mass index<18.5 kg/m^2^).Functional ambulation category^*^ (FAC) 2 or lower.Severe comorbidities (American Society of Anesthesiologists (ASA) category 4 or 5).

Patients and/or proxies who do not have sufficient comprehension of the Dutch language will be excluded from the interviews during phase 3.

*The FAC is a functional walking test that evaluates ambulation ability.^17^ This 6-point scale assesses ambulation status by determining how much human support the patient requires when walking, regardless of whether or not they use a personal assistive device. FAC≤2 means that a patients at least has the need for (intermittent) help of another person to be able to ambulate (FAC 2) to no functional ambulatory capabilities (FAC 0).

### Implementation in four phases

#### Phase 1 (exploration): evaluate current practice and identify facilitators and barriers of NOM implementation

Based on the evidence-based ‘Measurement Instrument for Determinants of Innovations’)^18 19^ and the ‘Barriers and Facilitators Assessment Instrument’, 20 a survey has been developed, aimed to identify the facilitators and barriers for applying SDM and NOM for selecting the best treatment for individual patients of the target population and identified five barriers and 23 facilitators.^9^ The patient perspective was not included in this study but was explored in another study.^11^ A panel from older adults organisations, general practitioners and geriatric specialists will discuss and supplement the data from the aforementioned studies from their perspective.

#### Phase 2 (installation): developing an implementation strategy for NOM

A draft protocol for NOM implementation, with as focal point the SDM interview, has been written based on the experience and expertise of the project members, previous studies and questionnaires. This protocol contains the central vision, the requirements for the implementation of NOM in selected frail older adults and a recommendation for the composition of a local project team of stakeholders and drivers of change. To remove barriers, practical tools such as pocket cards, posters, factsheets and local training options will be drafted or updated by the project team, based on the ‘Expert Recommendations for Implementing Change strategies’.^21^ This should help drivers of change in achieving implementation goals and change day-to-day policies. The NOM implementation protocol will contain an overview of the data to be collected for NOM evaluation. A reporting tool will be developed in the Dutch Hip Fracture Audit (DHFA) for this purpose. In addition, educational modules for healthcare professionals will be developed using the NOM protocol in combination with existing educational modules on SDM.^22–24^ NOM as a treatment option for selected frail older adults will also be included in the obligatory curriculum for residents by the Association of Surgeons of the Netherlands (in Dutch: Nederlandse Vereniging voor Heelkunde), in order to incorporate NOM into the educational programme of (orthopaedic) trauma residents.

#### Phase 3 (initial implementation): NOM-implementation in selected hospitals

NOM for selected frail older adults will be implemented in 14 selected hospitals (figure 2, collaborators listed in online supplemental materials 1). Based on the experience of these hospitals, the NOM implementation protocol and/or the educational material will be optimised. To safeguard implementation of NOM in the long term, the NOM protocol pays explicit attention to the involvement of all relevant healthcare providers by informing those involved before, during and after implementation, and by collecting data on relevant feasibility parameters as described in the Bowen model.^25^ To achieve this, the site principal investigator will be asked to establish a local project team. The team should represent all groups involved in NOM, including relevant physicians and, as applicable, residents of the involved departments, specialised nurses, physician assistants and hospital management. Prior to implementation, this local team will meet with the researchers for an interview to train them in applying the SDM and the NOM implementation protocol, and to collect details on their specific needs for the implementation.

10.1136/bmjopen-2023-083429.supp1Supplementary data

**Figure 2 F2:**
[figure not shown]
Map of participating hospitals during the initial implementation in selected hospitals (phase 3).

The local team will perform patient selection and apply SDM on NOM and operative treatment for all patients who meet the eligibility criteria. After the start of the implementation, during the first 6 months, patients, relatives and/or next-of-kin will be approached once by telephone to ask about their satisfaction with the treatment decision process and the chosen treatment. This will be done through a semistructured interview. To provide more insight about their own patient population, the interview results will be discussed with the participating centres on a quarterly basis. All collected data will be used to improve the NOM protocol and/or educational material prior to phase 4. Six months after start of implementation, the local team will be approached again for an interview to evaluate the process with the relevant parameters: adoption, integration, applicability, expansion and early local effectiveness.

#### Phase 4 (nationwide implementation): NOM-implementation in all hospitals in the Netherlands and project analysis

Phase 4 is an expansion of phase 3 to reach nationwide implementation. The implementation strategy will essentially be the same as in phase 3. Due to the increase in number of hospitals, the supervision and contact with the researchers and steering committee will be less intensive than in phase 3. In practice, this means that the NOM protocol will be implemented, but the interviews with healthcare professionals in the hospitals (prior to start and 6 months after start) will be omitted. To ensure that all information on SDM and NOM implementation is available continuously to both patients and healthcare providers, a dedicated website will be developed and maintained. To effectively reach a broad audience of healthcare providers and keep them updated on the implementation process and learning experiences, our goal is to give presentations at the annual meetings of orthogeriatric scientific associations, as well as associations for general practitioners and elderly care physicians (table 3). In addition, time slots for presentations will be requested at the meetings of the regional trauma networks. Ultimately, we aim to include SDM on NOM or operative treatment for proximal femoral fractures in select frail older adults in the National guidelines for hip fracture treatment and operative care in older adults.

### Outcome measures and data collection

The primary outcome measure (for phases 3 and 4) is (change in) the NOM rate. Type of treatment (NOM vs operative treatment) will be extracted from the DHFA. The DHFA is a national database, including over 95% of Hip fracture patients and can provide automated anonymous patient data up to 1 year after hip fracture treatment. To evaluate the effect of the implementation, the change in NOM rate and operative rate for the targeted population will be evaluated and compared with the rate prior to implementation. This will be calculated using the annual national DHFA data from the 2 years preceding implementation per hospital, as baseline. The postimplementation NOM rate will be collected immediately after completion of phase 4, as well as at the end of 2025. The secondary outcome measures (for phase 3 only) will be collected during semistructured interviews with patients/proxy or next-of-kin, 4–6 weeks after inclusion. These are the satisfaction with the chosen treatment on a numeric rating scale (0–10), their valuation of the information received during the SDM process, and if the patient’s needs were respected enough in the treatment decision. The interview sheets (in Dutch), used for patient or healthcare provider interviews in phases 1–3, are included in online supplemental materials 2.

10.1136/bmjopen-2023-083429.supp2Supplementary data

The following patient data will be also collected in phases 3 and 4 from the DHFA at 3 months and 1 year after hip fracture treatment (emerging from the patients’ medical records). Patient characteristics (age, sex, ASA, FAC), prefracture situation (residence, mobility, Katz Activities of Daily Living (ADL) score), fracture details (fracture classification, affected side), hospital details (hospital length of stay and intensive care length of stay) and outcome details (complications, revision surgeries, readmission, 30-day mortality and time until death).

Data will be collected for each patient who meets the eligibility criteria. To reduce the administrative burden, the DHFA database will be used as much as possible. Data from the DHFA will be imported in a Castor EDC database, in which hospitals can only see their own data. The datasets of all hospitals will be combined for the final analysis.

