### Statistical analysis

Data will be analysed by using the SPSS V.28 or higher (SPSS). Normality of continuous data will be tested with the Shapiro-Wilk test, and homogeneity of variances will be tested using the Levene’s test. A p<0.05 will be taken as threshold of statistical significance. Missing values will not be imputed.

The primary outcome, NOM rate, will be determined by dividing the number of patients treated with NOM by the total eligible number of patients (per participating centre and for all participating centres combined).

All continuous data will be reported as mean with standard deviation (SD; if normally distributed based on Shapiro-Wilk test) or as median with quartiles (if not normally distributed). Categorical data will be reported as number with percentage. Preimplementation and postimplementation data will be compared with a Student’s t-test (continuous data, normally distributed), Mann-Whitney U-test (continuous data, non-normally distributed), or a χ^2^ or Fisher’s exact test (categorical data), as applicable. The analysis will be stratified by NOM versus operative treatment, and further stratified as feasible depending on the final study population, for example, by time since NOM implementation, prefracture mobility, ADL status, fracture classification or bilateral fracture.

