### Project timeline

Phase 1 of the study started in June 2023 and ended in August 2023. Phase 2 started in June 2023 and ended in October 2023. Phase 3 started in September 2023 and will approximately end in October 2024. Phase 4 will start in June 2024 and will approximately be concluded in June 2025.

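### The primary before-after comparison of NOM rates has no calendar-time term or comparator, so any background trend is counted as the effect of implementation

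*Protocol article*

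**What the plan says.** Under Outcome measures and data collection, "The primary outcome measure (for phases 3 and 4) is (change in) the NOM rate". The same section sets the contrast from which the programme's effect is to be read: "the change in NOM rate and operative rate for the targeted population will be evaluated and compared with the rate prior to implementation". The reference is "annual national DHFA data from the 2 years preceding implementation per hospital, as baseline". The post-implementation rate is taken once phase 4 is complete and again at the end of 2025.

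Under Statistical analysis, "Preimplementation and postimplementation data will be compared with a" two-sample test. For a categorical outcome such as treatment type this is chi-square or Fisher's exact test, at p<0.05. The NOM rate is calculated per centre and for all centres combined. The only time element is an optional stratification by time since implementation.

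The change is given a causal label. The last row of Table 2 presents it as measuring the effect of implementation, and Table 3 says that the DHFA data before and after "will thus allow accurate monitoring of the impact of NOM implementation".

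The Introduction says that "a paradigm shift is occurring in clinical approach", that several hospitals have already asked for guidance, and that a protocol version has already been piloted. Under Project timeline, phase 3 started in September 2023 and runs to about October 2024, while "Phase 4 will start in June 2024" and runs to about June 2025. The aim given in Table 2 for the phase 3 association presentations begins "Creating awareness and a sense of urgency for SDM implementation".

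**The concern.** A two-sample test of before against after answers whether the rate changed, not why. With no calendar-time term and no concurrent comparator, a trend unrelated to the programme and the effect of the programme are added together, and the sum is named the effect. Strengths and limitations does not mention secular trend. It discusses only possible under-measurement of NOM through decisions made before hospital.

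A second problem works in the opposite direction. Hospitals that start in June 2024 or later take part of their two-year baseline from months in which phase 3 was running and awareness presentations were planned. If those presentations changed practice, the baseline already holds some of the effect and the measured change is too small.

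At stake is how the primary outcome is interpreted. The Discussion expects the rate to rise and hopes the results will inform guidelines, yet the planned test cannot tell whether the programme caused a rise. The data that could help are already planned for: the DHFA is national, covers over 95% of hip fracture patients, and hospitals start at different times.

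**Working it through.** **1. The article's own figure.** Sample size calculation gives 17,225 patients aged 70 or older, about 25% of them in a nursing home or other institution: 0.25 × 17,225 = 4,306, against the stated 4,300. About half meet the criteria, so about 2,150 per year. Two baseline years give 4,300 patients and one later year gives 2,150. No NOM rate, trend or target effect is stated; these are assumptions below.

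**2. Size of the bias.** Spurious change = annual trend × years between window midpoints. A two-year baseline is centred 1 year before the start, and a one-year window after the start is centred 0.5 years after it, so the gap is 1.5 years. At 2 points per year the spurious change is 2 × 1.5 = 3.0 points.

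**3. Probability that the planned pooled test is significant with no implementation effect.** This is Φ[(d − 1.96·SE₀)/SE₁], where d is the spurious change, SE₀ uses the pooled rate and SE₁ the two separate rates.

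Worked at a 15% baseline, 15% to 18%:
- pooled rate = (0.15 × 4,300 + 0.18 × 2,150)/6,450 = 0.16
- SE₀ = √[0.16 × 0.84 × (1/4,300 + 1/2,150)] = 0.00968
- SE₁ = √[0.1275/4,300 + 0.1476/2,150] = 0.00991
- (0.03 − 0.01898)/0.00991 = 1.11, so Φ = 87%

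| Assumed baseline NOM rate | Rise of 2 points/year, gap 1.5 years | Same rise, gap 2.5 years |
|---|---|---|
| 10% | 95% | 100% |
| 15% | 87% | not calculated |
| 20% | 79% | 99.5% |
| 40% | 64% | 97% |

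At a 15% baseline and a 1.5-year gap, rises of 1 and 3 points per year give 35% and 99.5%.

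**4. Simulation of the roll-out.** Assumptions: 70 hospitals, 20% mean baseline rate, 14 starting late in 2023, 56 starting over four quarters from mid-2024, data to the end of 2025, a linear trend common to all hospitals and a constant effect; 300 runs per scenario. The comparison model has hospital and calendar-quarter effects and cluster-robust standard errors.

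| True effect, trend | Planned test: significant | Planned: mean change | Staggered model: significant | Staggered: mean estimate |
|---|---|---|---|---|
| 0, 0/year | 5% | 0.0 | 3% | 0.0 |
| 0, 1/year | 38% | +1.6 | 5% | +0.3 |
| 0, 2/year | 86% | +3.1 | 2% | +0.1 |
| 0, 3/year | 99% | +4.8 | 5% | 0.0 |
| 5, 2/year | 100% | +8.1 | 67% | +4.7 |

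**5. Baseline overlap.** For a start in June 2024 the baseline runs from June 2022 to May 2024. September 2023 to May 2024 is 9 of those 24 months. Later starts overlap by more, up to the 14 months from September 2023 to October 2024 given for phase 3.

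**6. Precision (95% half-widths).**
- Planned pooled contrast at 15%: 1.96 × √[0.1275 × (1/4,300 + 1/2,150)] = 1.8 points.
- The 14 pilot hospitals against not-yet-started hospitals, September 2023 to May 2024, if the 14 hold 20% of patients: 1.96 × √[0.1275 × (1/320 + 1/860 + 1/1,290 + 1/3,440)] = 1.96 × 0.0261 = 5.1 points, before between-hospital variation. Power for a true 5-point effect is Φ(0.05/0.0261 − 1.96), about 48%.
- Full-period model, from the simulated standard error of about 1.9 points: 1.96 × 1.9 = 3.7 points.

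**The case against.** The article gives no NOM rate and no trend. A reader might infer that NOM was already spreading in the data and that a background rise will be reported as the effect. The documents do not support that: the Introduction's evidence is qualitative, and the rejection probabilities depend on an assumed rise. Nor does Table 2 date the awareness presentations, so the 9 months is the possible overlap for a June 2024 start, not measured contamination. These limits stand, and the point is conditional for that reason.

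A reader might also infer that the nine-month contrast of the 14 hospitals with the rest should become the headline result. It should not. The primary outcome covers phases 3 and 4, the aim is national, and the early window catches local teams while the protocol is still being improved. That contrast is also about 2.8 times less precise than the planned one (5.1/1.8), with only about even odds of detecting 5 points. Switching every remaining hospital to exposed in June 2024 would also misclassify those that start later in a roll-out lasting to about June 2025.

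Finally, Table 2 words the aim of the phase 4 measurement as evaluating changes in practice, the Discussion says a higher NOM rate is not the main goal, and no patient's treatment depends on this p-value. That lowers the severity. It does not remove the point, because the article itself fixes the contrast and the test and names the result the effect. This is not detail left to an analysis plan, and stratifying by time since implementation does not separate calendar trend from effect.

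**Conclusion.** The point holds in conditional form and should be fixed. As planned, the primary comparison can show that the NOM rate changed but cannot attribute the change to the implementation. Any background trend is added to the result, at its annual size times the gap between windows. A rise of 2 points per year over 1.5 years would by itself give a 3-point change, significant in 64% to 95% of repetitions across baseline rates of 40% down to 10%. This assumes 4,300 versus 2,150 eligible patients, a two-sided 5% test and no implementation effect. Spill-over into the baseline of later hospitals would push the other way by an unknown amount, so the net direction of bias cannot be stated from the article. The Table 3 wording on accurate monitoring of impact goes further than the design allows. The simulated advantage of the staggered model rests on its assumptions of a trend shared by all hospitals and a constant effect.

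**What to change.** Keep the estimand for phases 3 and 4, and keep the raw before-after difference as a descriptive result. Base any statement about the effect of implementation on one patient-level model:

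- **Data:** DHFA records from all hospitals, from 24 months before the first start to the end of 2025.
- **Terms:** hospital effects, calendar quarter, and an exposure indicator switched on at each hospital's recorded start date. Use the phase dates only in a sensitivity analysis.
- **Adjustment and errors:** the case-mix variables already collected (age, sex, ASA, FAC, residence, Katz score), with standard errors that allow for clustering by hospital.
- **Supporting contrast, not the headline:** the 14 pilot hospitals against not-yet-started hospitals, September 2023 to May 2024.
- **Stated limits:** the 14 hospitals were selected, not randomised, and diffusion to later hospitals pulls the estimate toward zero.

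If this model is not used, report the change as descriptive, add secular trend to the limitations and withdraw the Table 3 claim about accurate monitoring of impact.

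The cost is modelling time, a recorded start date for each hospital, and a clearly wider interval. The naive pooled half-width is about 1.8 points at a 15% rate. The pilot-only contrast is about 5.1 points before between-hospital variation. The full-period model should fall between them (about 3.7 points in the simulation at a 20% rate). No new patient outcome data are needed.
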